#### Secondary outcomes

The secondary outcomes are as follows:OS refers to the length of time from randomization to mortality from any cause. In cases where no information on mortality is available in the clinical database, the last date on which the patient is known to have survived is used as the cut-off point.The DCR indicates the percentage of patients who have achieved CR, partial remission (PR), and disease stabilization for over 4 weeks continuous, accounting for all the subjects with evaluable efficacy.The ORR is the proportion of patients who achieve CR or PR ([CR + PR]/total number of cases × 100%), as assessed by the RECIST v1.1 [30].Adverse events at levels 3 and 4: patients with adverse events at levels 3 and 4 will be assessed according to the National Cancer Institute Common Toxicity Criteria (NCI-CTC) Version 4.0 [32].

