**Methods/analysis:**

This study is a triple-blind, randomized, placebo-controlled, parallel-group clinical trial. We plan to include 238 female patients with locally recurrent or metastatic TNBC, admitted to the Liaoning Cancer Hospital & Institute, Northeast China. All enrolled patients will be randomized to oral vinorelbine alone (40 mg, thrice a week (Mondays, Wednesdays, and Fridays) in each 3-week cycle), or in combination with oral apatinib mesylate (500 mg, once daily in each 3-week cycle). Radiographic assessment will be performed every 6 weeks for 36 weeks and every 9 weeks thereafter. The primary outcome is progression-free survival and secondary outcomes include overall survival, disease control rate, objective response rate, and incidence of adverse events at grades 3 and 4, as defined by the National Cancer Institute Common Toxicity Criteria Version 4.0. Outcome measures will be evaluated at baseline (< 2 weeks before starting treatment), every 6 weeks during treatment, and at 4 weeks and every 3 months after treatment discontinuation.

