### Statistical analysis

The primary analysis will be based on the intent-to-treat (ITT) principle (i.e. all patients will be analyzed according to their allocated treatment group). Missing primary endpoint data will be imputed conservatively. We will consider a sensitivity analysis using complete case, i.e. not imputing missing values, to assess if there is a difference in results. No interim analysis will be performed.

A statistician will perform the statistical analyses using SPSS 22.0 software (IBM, Armonk, NY, USA). Continuous variables will be summarized as the mean, standard deviation, median, minimum, and maximum. Means and standard deviations will be reported if the variable is normally distributed; if the data are skewed, medians and interquartile ranges will be used. Categorical variables will be expressed as numbers and percentages.

The baseline data will be summarized accordingly, depending on the data type (continuous, categorical). Categorical variables will be compared between groups using Pearson’s chi-square test. Continuous variables will be compared between groups using the two-sample *t* test (normally distributed data) or Mann-Whitney U test (non-normally distributed data). All statistical analyses will be performed based on a two-sided test. A *P* value ≤0.05 will be considered statistically significant, and the 95% CI will be calculated.

Survival data (PFS and OS) will be estimated using the Kaplan-Meier method. Differences between grouped survival profiles will be assessed by the log-rank test. Factors influencing survival (i.e., age, tumor, node, metastasis (TNM) staging, tumor differentiation status, lymph node metastasis, and chemotherapy cycles) will be analyzed using Cox proportional hazard regression analysis. Results will be expressed as HRs and 95% CIs.

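### DCR is taken over evaluable patients while ORR is taken over all cases, and the severe-toxicity endpoint stops at grade 4

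*Protocol article*

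**What the plan says.** The Secondary outcomes section of the protocol article defines both response endpoints. DCR counts complete response, partial remission and "disease stabilization for over 4 weeks continuous, accounting for all the subjects with evaluable efficacy"; the last words set its denominator. ORR follows directly: "The ORR is the proportion of patients who achieve CR or PR", with the formula "CR + PR]/total number of cases × 100" (per cent). The text does not say what makes a patient evaluable, or why the two denominators differ.

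The Statistical analysis section states the intent-to-treat principle for the primary analysis, explained as "all patients will be analyzed according to their allocated treatment group". It says nothing about the analysis set for DCR.

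The severe-toxicity endpoint appears twice. The Abstract (Methods/analysis) gives "incidence of adverse events at grades 3 and 4", and the Secondary outcomes section gives "Adverse events at levels 3 and 4: patients with adverse events at levels 3 and 4 will be assessed". Neither mentions grade 5.

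**The concern.** ORR is CR plus PR, and DCR is CR plus PR plus stable disease. Readers expect the difference between them to be the stable-disease rate. With different denominators it is not.

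The DCR denominator also depends on what happens after randomisation. Eligibility already requires measurable disease, so a correctly enrolled patient becomes non-evaluable mainly through lack of a usable later assessment. Those who leave before the first scan are unlikely to be a random subset. If they are removed, DCR describes patients who stayed long enough to be scanned. If the two arms lose different proportions, the randomised comparison for this endpoint is no longer protected.

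The toxicity endpoint has a related but smaller gap. As worded, a patient with a fatal event and no recorded grade 3 or 4 event does not count as having had severe toxicity.

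**Working it through.** The plan states no DCR or severe-toxicity figure, so there is nothing to reproduce. The check compares the definitions and then shows how much they could matter.

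**Can patients leave before any efficacy scan?**
- Imaging on treatment is every 6 weeks (Abstract; During treatment section).
- Under the Dose adjustment section, exceeding the pause limits, or a delay of at least 2 weeks in the next cycle, leads to withdrawal. Cycles last 3 weeks, so a delay of cycle 2 can reach that limit at 3 + 2 = 5 weeks, before the first scan.
- The Follow up section lists no imaging at the visit 4 weeks after stopping. The 3-monthly follow-up records progression status but lists no scan.

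So a patient who leaves before week 6 may have no scheduled post-baseline image.

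**Effect on DCR.** Let d be the proportion of all randomised patients with disease control, and u the proportion not evaluable, all without recorded disease control. The evaluable-only rate is d/(1 − u). The value d = 60% in both arms and all the u values are assumptions. The only related figure in the article is the 10% dropout allowance across both groups in the Sample size section, which is not a rate of non-evaluability.

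| Not evaluable, apatinib / placebo | Reported DCR, apatinib | Reported DCR, placebo | Apparent difference (true 0) |
|---|---|---|---|
| 10% / 10% | 0.60/0.90 = 66.7% | 66.7% | 0 |
| 15% / 5% | 0.60/0.85 = 70.6% | 0.60/0.95 = 63.2% | +7.4 points |
| 20% / 5% | 0.60/0.80 = 75.0% | 63.2% | +11.8 points |
| 5% / 15% | 63.2% | 70.6% | −7.4 points |

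**A different starting point.** Take 119 per arm and a DCR of about 77.3% among evaluable patients in both arms. That is the rate Table 1 gives for a retrospective vinorelbine-plus-cisplatin group and is used only as an illustration.
- With 10% not evaluable in each arm: 83/107 = 77.6% among evaluable patients, 83/119 = 69.7% among all randomised.
- With 15% not evaluable on apatinib and 5% on placebo: 78/101 = 77.2% versus 87/113 = 77.0% among evaluable patients, a difference of +0.2 points. Over all randomised it is 78/119 = 65.5% versus 87/119 = 73.1%, a difference of −7.6 points. The evaluable-only rate hides this.

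**Nesting.** With R responders, S patients with stable disease, E evaluable and N randomised, DCR − ORR = (R + S)/E − R/N = S/E + ORR × (N/E − 1). At 10% non-evaluable, N/E − 1 = 1/0.90 − 1 = 0.111, so the gap overstates the stable-disease rate among evaluable patients by one ninth of the ORR.

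**Toxicity endpoint.** Each patient whose only severe event is fatal is worth 1/119 = 0.84 points of an arm's rate. If 1% to 5% of an arm had a fatal adverse event (assumed), that is about 1 to 6 of 119 patients. The uncounted number is smaller if some of them had an earlier grade 3 or 4 event.

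**The case against.** Several points on the other side stand.

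- A reader might infer that the DCR definition contradicts the plan's intent-to-treat commitment. It does not. That commitment, and the conservative imputation that goes with it, is made for the primary analysis, which is PFS. An evaluable-patient denominator departs from that approach but breaks no stated rule.
- Neither evaluable efficacy nor the ORR's total is defined. An early death could be classed as progression and stay in the DCR denominator, and a patient who stops for toxicity could still be scanned. The wording permits the exclusion; it does not show that it will happen.
- A reader might infer that the bias favours apatinib. The article gives no non-evaluable rate by arm. With equal true rates and equal losses both arms are inflated alike and no false difference appears. Early progression or death on placebo could remove more controls and reverse the sign.
- A reader might infer that fatal events are lost from the trial. They are not. The Adverse events section has all adverse events recorded and on-study deaths reported, and death from any cause counts in PFS and OS. Nor would a fatal event lower the recorded severe-event rate; it would fail to raise it, and only in a patient with no earlier grade 3 or 4 event.

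One further defence is that a condensed article leaves analysis sets to the full protocol or SAP. That would excuse silence. Here the article states a denominator for each endpoint, and the two differ.

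**Conclusion.** The point holds in limited form. Two nested response endpoints have different stated denominators, and the one for DCR allows an exclusion after randomisation that the visit schedule makes plausible. The consequence that needs no imbalance between arms is an inflated DCR in each arm, from 60% to 66.7% at an assumed 10% non-evaluable. Distortion of the comparison is conditional: about 7 points in either direction for an assumed 5% versus 15%, and none if losses and true rates are equal.

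The toxicity endpoint, as worded in two places, does not count a patient whose only severe event is fatal, at about 0.8 points each. This is a gap in one endpoint, not in safety data collection. Neither matter touches the PFS analysis or the sample size of 238.

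**What to change.** - Define the DCR denominator as all randomised patients, state the same for ORR, and count non-evaluable patients as not having disease control. Keep the evaluable-only rate as a supportive analysis, with evaluable defined and the number not evaluable shown by arm and reason.
- In the Abstract and the Secondary outcomes section, change the toxicity endpoint to grade 3 or higher, including grade 5, with fatal events also shown separately.

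The cost is a change of wording, best made before unblinding, using data the trial already plans to collect. The reported DCR will be lower where any patients are non-evaluable, and the severe-event rate may be slightly higher.

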#### Other measures

Other measures will be performed as follows:Quality of life will be assessed using the EORTC QLQ-C30 version 3.0 [33]. The scores will be averaged and transformed linearly to obtain a range of scores, from 0 to 100, with higher scores indicating better quality of life.General health status is assessed using the ECOG-PS scale [34]. The scale divides the patient’s activity status into 0–5 levels. A higher level indicates a worse physical status.Laboratory examination: (1) hematology assessments: hemoglobin, white blood cell count, neutrophil count, and platelet count; (2) blood biochemical tests: total bilirubin, ALT, AST, alkaline phosphatase, serum creatinine, total protein, Na^+^, K^+^, Mg^2+^, Cl^−^, Ca^2+^, urea, and pregnancy test (if applicable); and (3) tumor marker detection: CA153 and CEA.

### Adverse events

All adverse events will be recorded appropriately in a case report form and assessed by the investigators according to the NCI-CTC version 4.0 [32]. If the level of ALT or AST is ≥ 3 × ULN, or total bilirubin ≥ 2 × ULN, a serious adverse event (SAE) report may be necessary. The investigators must promptly determine whether the patient meets Hy’s Law (drug-induced liver injury (DILI)), without delay.

The investigators will assess the causal relationship between adverse events and target drugs. The decisive factor in the assessment is the temporal correlation between the adverse event and target drug. All deaths during the intervention period, and during the last follow-up period (30 days after the last dose) and the period up to documented disease progression (whichever occurs later) will be reported.

The investigator is obliged to immediately (within 24 h) call, fax, or email information on any serious or medically significant clinical adverse events or laboratory abnormalities during the study period, to the Adverse Drug Reaction Monitoring Center, the Sponsor, and the Ethics Committee. This applies regardless of group allocation. Optimal supportive therapy will be provided in cases of hematological toxicity, non-hemotoxic diarrhea, liver toxicity, and peripheral neurotoxicity.

### Criteria for re-administration/cycle delay

Patients who meet all of the following criteria can receive the planned treatment:Absolute neutrophil count (ANC) > 1500/mm^3^Platelets > 100,000/mm^3^Treatment related to non-hematologic toxicity has been eliminated at baseline or is at a level ≤ 1 (except for level-2 alopecia or level-2 fatigue)

If the patient cannot meet these criteria, the planned treatment will be delayed and the patient’s condition will be re-evaluated at least once a week.

Additional criteria for re-administration/cycle delay are as follows:The medication on the 8th day of each cycle cannot be delayed for longer than 1 week, otherwise, the patient will be withdrawn from the study. The time of medication administration in the next cycle will not change.In the case of failure to recover from treatment-related toxicity to baseline or level 1 (except level 2 and level-2 fatigue) within 3 weeks as scheduled (i.e., the start of each new cycle is delayed for over 21 days as compared with the scheduled time), the patient will be withdrawn from the trial.Patients can continue to use the drug, with the consent of the Sponsor, if the treatment is deemed to be effective.

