### Drug administration

Vinorelbine plus apatinib group: a 40 mg vinorelbine tartrate soft capsule (brand name Navelbine, registration number H20140657; Pierre Fabre Medicament, Boulogne, France) is administered orally in the morning (at least 1 h before, or at least 1 h after meals), three times a week (Mondays, Wednesdays, and Fridays), for a continuous 21-day cycle. A 500 mg apatinib mesylate tablet (brand name Aitan; state medical permission number. H20140103), is administered orally once a day for a continuous 21-day cycle.

Vinorelbine plus placebo group: oral administration of vinorelbine will be the same as in the vinorelbine plus apatinib group. In addition, the patients will be given oral placebo (starch as an ingredient). The placebo appearance, including shape, size, color and weight, taste, labeling, and packing is the same as that of the apatinib mesylate tablets.

The placebo and the apatinib will be manufactured by Jiangsu Hengrui Pharmaceutical Co., Ltd., China in accordance with the guidelines of Good Manufacturing Practice (Chinese Edition). The manufacturer will have no direct involvement in the study (apart from the drug manufacturing and delivery to the clinical trial centers). An assessment will be conducted at the end of every second cycle of the described administration protocol, until unacceptable toxicity or disease progression is observed.

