### Dose adjustment

Principle for dose adjustment: in the case of adverse events associated with apatinib, the dose will be adjusted first (Table 2). There are two dose levels for apatinib: (1) initial dose: 500 mg, once daily; (2) secondary dose: 250 mg, once daily. Medication will be paused if the patients cannot recover from drug toxicity. The time for each pause and the cumulative time of overall pauses per cycle are limited to 1 week. There is a maximum of two pauses per cycle, to ensure the medication intensity in each patient. Patients not meeting the above criteria, or having a delay of the subsequent treatment cycle of at least 2 weeks, will be required to withdraw from the trial.

**Table 2 Tab2:** Principle for the adjustment of apatinib dose

Classification of adverse reactions	NCI-CTC level	Dose adjustment
Hematologic adverse reactions	3	Drug administration will be paused at level 3 and will be continued at the initial dose when the NCI level is restored to ≤ level 2. If NCI ≥ level 3 occurs again, drug administration at the secondary dose will be continued
	4	Drug administration will be paused at level 4 and will be continued at the secondary dose when the NCI is ≤ level 2
Non-hematologic adverse reactions	3	Drug administration will be paused at level 3 and will be continued at the initial dose when the NCI is restored to ≤ level 1. If the NCI ≥ level 3 occurs again, drug administration at the secondary dose will be continued
	4	Drug administration will be paused at level 4 and will be continued at the secondary dose when the NCI is ≤ level 1

Adverse reactions will be assessed using the National Cancer Institute Common Toxicity Criteria (NCI-CTC) Version 4^30^

The dose of apatinib can be adjusted at any time during each dosing cycle. Once the dose is reduced, however, a subsequent increase to the previous level is not permitted. Only a single dose adjustment is allowed for each subject. After the dose is decreased to 250 mg, no further dose adjustments are permitted for any reason. However, pausing of medication administration will still be permitted.

When any conditions that meet the criteria for drug withdrawal are observed, administration of vinorelbine will be discontinued. If the patient meets the criteria for drug re-administration in the subsequent cycles, vinorelbine administration will be resumed, but the doses that are not taken during the withdrawal period will be omitted (Table 3).

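### The study-withdrawal rule for a delayed day-8 medication matches no day-8 administration in the regimen, and a long vinorelbine hold can be read as study exit or as resumption

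*Protocol article*

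**What the plan says.** All references are to the protocol article.

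- **Drug administration.** Vinorelbine is taken "three times a week (Mondays, Wednesdays, and Fridays), for a continuous 21-day cycle". Apatinib "is administered orally once a day for a continuous 21-day cycle", and the control group takes a matching placebo. No administration is specific to day 8.
- **Dose adjustment, vinorelbine paragraph.** "When any conditions that meet the criteria for drug withdrawal are observed, administration of vinorelbine will be discontinued". Then: "If the patient meets the criteria for drug re-administration in the subsequent cycles, vinorelbine administration will be resumed", and "the doses that are not taken during the withdrawal period will be omitted". The triggers are in Table 3 and include level 3 or 4 neutrophil or platelet toxicity.
- **Dose adjustment, apatinib paragraph.** Each pause, and all pauses in a cycle together, may last at most 1 week, with at most two pauses per cycle. Patients outside these limits leave the trial.
- **Criteria for re-administration/cycle delay.** "The medication on the 8th day of each cycle cannot be delayed for longer than 1 week, otherwise, the patient will be withdrawn"; the withdrawal is from the study. The next sentence reads: "The time of medication administration in the next cycle will not change". A separate rule covers late cycle starts. A last item allows continued use with the sponsor's consent if treatment is judged effective.

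**The concern.** A rule that names day 8 suits a schedule with a defined day-8 dose. This trial has none, and the sentence does not say whether it means vinorelbine, apatinib or placebo, or both. It treats the day-8 medication as something that can be postponed, whereas Dose adjustment drops held vinorelbine doses and restarts the drug later. Two investigators facing the same toxicity could follow the text and do opposite things.

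For the analysis, the issue is what happens to a patient who exits under this rule. The trigger is toxicity, so if exit also meant no further assessment, progression-free survival (the primary outcome) and overall survival would be censored for a treatment-related reason.

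**Working it through.** The plan states no figure to reproduce. The check applies the rules to the dosing calendar.

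**1. Dosing days.** Three per week × 3 weeks = 9 vinorelbine days per cycle, whatever the start weekday. With a Monday start they are days 1, 3, 5, 8, 10, 12, 15, 17 and 19. Day 8 falls on the same weekday as day 1. It therefore carries vinorelbine only if the cycle starts on a Monday, Wednesday or Friday. With any other start, vinorelbine has no day-8 dose.

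**2. When the day-8 rule is met.** Delay = resumption day − 8, if the hold covers day 8. The rule needs a delay above 7 days. Resuming on day 15 gives 15 − 8 = 7, which is not longer than a week. With a Monday start the next dosing day is 17, and 17 − 8 = 9, which is. The next cycle starts on day 22 and its timing does not move, so resuming then gives 22 − 8 = 14.

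**3. Examples (Monday start, vinorelbine).**

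| Hold from | Resume on | Hold length (days) | Doses missed | Day-8 delay (days) | Day-8 rule | Dose adjustment, vinorelbine paragraph |
|---|---|---|---|---|---|---|
| 5 | 15 | 10 | 4 | 7 | not met | doses omitted |
| 8 | 17 | 9 | 4 | 9 | study withdrawal | doses omitted |
| 5 | 22 | 17 | 7 | 14 | study withdrawal | resume, doses omitted |
| 8 | 22 | 14 | 6 | 14 | study withdrawal | resume, doses omitted |
| 10 | 22 | 12 | 5 | none | not met | resume, doses omitted |

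The rows for resumption on day 22 are exactly the case that Dose adjustment describes, resumption in a later cycle. For holds from day 5 or day 8 the two sections disagree. The 9-day hold from day 8 meets the rule and the 12-day hold from day 10 does not, although the second is longer and misses more doses.

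**4. Does the 1-week pause limit settle it?** For apatinib or placebo, largely yes. A pause that makes the day-8 medication more than 7 days late is itself longer than 7 days, so both sections point to exit. For vinorelbine it is unclear, because the limit stands in the paragraph on apatinib dose levels. If it also covers vinorelbine, a hold lasting until day 22 is allowed only if it starts on day 15 or later (22 − 15 = 7; 22 − 12 = 10). That is hard to square with an unqualified sentence on resuming in subsequent cycles.

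**The case against.** The strongest reply is that no conflict exists. Read literally, a dose that is omitted is not delayed, so a vinorelbine hold under Dose adjustment never engages the day-8 rule. If the 1-week pause limit covers both drugs, a longer hold ends in withdrawal under either section. The sponsor-consent item also lets patients continue.

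Part of this stands. Each reading is possible, and for apatinib or placebo the sections mostly agree. But the first reading leaves the day-8 rule with no effect on a vinorelbine toxicity hold, and the second empties most of the resumption sentence. The document does not choose between them. The consent item is discretionary, depends on judged efficacy, and does not say that it overrides the day-8 rule.

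The objection on follow-up is well founded. A reader might infer that the rule removes patients from progression-free and overall survival follow-up, and more of them in the more toxic arm. The documents do not support this. The Follow up section collects progression and survival status every 3 months after treatment discontinuation until death or study completion. The Statistical analysis section analyses all patients as allocated. The Participant withdrawal section lists consent withdrawal, patient request, and declining treatment or follow-up, but not toxicity delay. What remains is an ambiguity in the phrase on withdrawal from the study.

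**Conclusion.** The point holds as an internal inconsistency. The day-8 rule fits no administration that the regimen defines, names no drug, and can be read against the resume-and-omit rule for vinorelbine. The conflict is confined to vinorelbine holds that cover day 8 and continue more than 7 days past it. The worked examples assume a Monday cycle start. They also treat a dose missed on day 8 as delayed until the drug is resumed.

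The number of patients affected cannot be computed. A reader might try: with a Monday start, 4 of the 9 dosing days fall on or before day 8, so an assumed 10% to 30% of patients with one hold would give 0.10 × 4/9 × 238 = 11 to 0.30 × 4/9 × 238 = 32 exits, against a 10% dropout allowance of about 24. The hold rate has no source in the document. The sum also assumes evenly spread holds that all last until day 22, and it counts day-1 holds that the separate cycle-delay rule may govern. Dropping those alone gives 3/9, or 8 to 24. These figures should not be used.

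The effect on the primary analysis is a risk that depends on how withdrawal is read. It is not a demonstrated bias.

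**What to change.** Reconcile Drug administration, Dose adjustment, and Criteria for re-administration/cycle delay so that a held dose of each drug has one consequence under the schedule actually given. The text should say which drug each rule covers, whether the 1-week pause limit applies to vinorelbine, and how the sponsor-consent item relates to the withdrawal rules. Which rule stays, and what the limit is, is for the clinical team.

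Add one sentence stating that patients taken off treatment under these rules remain in follow-up for progression-free and overall survival, as the Follow up and Statistical analysis sections already plan.

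The cost is a short text amendment, which the protocol requires the ethics committee to approve. The sample size, randomization and analysis method do not change.
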